#### Interventional product: FMT and placebo capsules

The study product consists of FMT capsules prepared by [name] team in London, Ontario, Canada. [name] has received approval from Health Canada to prepare FMT and placebo capsules for the Gutsy study (Control #292512).

Thirty to forty capsules, depending on the fiber content of the donor’s feces, are prepared from 80 to 100 g of healthy human feces from a single healthy donor, encapsulated in triple layer gelatin capsules. A total of 30 to 40 capsules are administered as a single dose. Capsules are prepared following a modified method as described by Kao et al. and [name] group [30, 35, 39–43]. Capsules are shipped to Montreal on dry ice and stored at −80 °C until use. Capsules from the same donors are given at visits 3 and 4.

Placebo capsules contain microcrystalline cellulose for equivalence in weight and color, also encapsulated in triple layer gelatin capsules. Placebo capsules are shipped and stored at room temperature until dispensation.

### Criteria for discontinuing or modifying allocated interventions {11b}

Discontinuation or modification of the allocated interventions may occur in the following situations: vomiting during capsule intake, adverse events (AEs), abnormal laboratory findings, and investigator judgment.

Vomiting during capsule intake: If a participant vomits during or shortly after taking the FMT or placebo capsules, the investigator will evaluate the reason and a decision will be made to either repeat dosing or exclude the participant from further treatment.

Adverse events (AEs): If a participant experiences persistent or clinically significant adverse events after the first dose, the second dose will not be administered. The participant will continue follow-up visits to monitor and resolve the AE, but no further study product will be given.

Abnormal laboratory findings: If abnormal lab results persist following the first dose, the second dose will not be administered. The participant will be referred for appropriate medical follow-up.

Investigator judgment: The investigator may discontinue the intervention at any point based on clinical judgment regarding safety.

### Strategies to improve adherence to interventions {11c}

To ensure the integrity of the study, adherence to both the fecal microbiota transplantation (FMT) or placebo regimen and antiretroviral therapy (ART) will be rigorously monitored by:Direct observation of capsule intake: All participants take the FMT or placebo capsules under direct supervision by trained study staff at the study site. This ensures complete adherence to dosing on both treatment days (day 0 and day 22).Ongoing communication and counseling: Participants are educated about the importance of adherence to both study procedures and their ongoing ART. Study staff follow up and maintain communication with participants throughout the study.Scheduling support and reminders: Participants are provided with clear scheduling, instructions, and reminders for upcoming visits and stool/blood collection.

### Relevant concomitant care permitted or prohibited during the trial {11d}

#### Permitted concomitant care and medications

All participants must continue their ART throughout the entire study period.Concomitant medications, supplements, natural remedies, and foods are generally permitted except those explicitly listed in the exclusion criteria.Use of non-prescription drugs is allowed if approved by the investigator and must be documented.

#### Prohibited or restricted concomitant care and interventions

Excluded at screening (and thus effectively prohibited during the trial):Use within the past 3 months of antibiotics, prophylactic antibiotics, immune-modulatory agents, and morphine. These substances are excluded due to their effects on gut microbiota.Recent changes in dietary habits, intermittent fasting, chronic constipation, or laxative use. These can significantly affect gut microbiota and interfere with outcomes.Current participation in an experimental therapy study or receipt of such therapy in the last 6 months.During the study:Participants are asked to refrain from consuming non-prescription drugs for 48 h prior to each study visit, unless pre-approved by the investigator.Alcohol use should be limited to a maximum of one alcoholic drink per day, preferably less than daily as alcohol negatively modulates gut microbiota and increases inflammation.Participants should refrain from cannabis and limit alcohol (no more than one drink with dinner) in the 24 h prior to each study visit.Street drug use and cigarette smoking: not outright prohibited, but surveyed at each visit and may influence continued participation based on investigator’s judgment.At investigator discretion:Any new medication or procedure must be reported.The investigator evaluates whether it may interfere with study interpretation and may lead to withdrawal if necessary.

### Provisions for post-trial care {30}

FMT capsules will not be provided at the end of the study, as clinical benefits will have not yet been demonstrated. This means participants will not continue receiving FMT post-study, even if they benefited from it during the trial.

Participants who experience unresolved clinically significant AEs will be followed until resolution or stabilization. Monthly follow-ups may occur until resolution, and these will be documented in the electronic case report form (eCRF). Unscheduled visits can be scheduled as needed to monitor and manage AEs. If needed, participants will be referred to appropriate specialists. If a participant discontinues the study due to an AE, the investigator is responsible for their clinical follow-up and safety follow-up visits will be arranged, and participants may be referred for further care.

The study is conducted in accordance with ICH-GCP and Health Canada regulations, which requires reporting and medical management of harms. Should the participant suffer any harm following administration of the study drug or any other procedure related to the research study, he or she will receive all the care and services required by his or her state of health.

### Outcomes {12}

Table 1 is a structured summary of the primary, secondary, and exploratory outcomes, including the measurement variables, analysis metrics, methods of aggregation, time points, and clinical relevance.

**Table 1 Tab1:** Study outcome details

a. Primary outcome					
Outcome	Details				
Measurement variable	Plasma levels of REG3α (a marker of gut permeability)				
Analysis metric	Change from baseline compared between FMT and placebo groups				
Method of aggregation	Mean or median (analyzed using *t*-test or Wilcoxon rank sum test)				
Time points	Baseline (visits 2 and 3), week 6, and week 12				
Clinical relevance	REG3α is a key biomarker for gut epithelial damage and microbial translocation. Reducing REG3α suggests improved gut barrier integrity, which may decrease chronic immune activation in ART-treated PWH				
b. Secondary outcomes					
Outcome	Measurement variable(s)	Analysis metric	Method of aggregation	Time points	Clinical relevance
Safety and tolerability of FMT	Adverse events, hematology, serum chemistries (e.g., ALT, AST, glucose, lipids, hs-CRP, D-dimer)	Incidence/frequency; change from baseline, compared between FMT and placebo arms	Proportion; mean/median	Throughout study (all visits)	Evaluates whether FMT is safe and well tolerated in PWH
Markers of gut permeability	Plasma I-FABP, LPS, β-D-glucan	Change from baseline, compared between FMT and placebo arms	Mean/median (Multiplex, ELISA, Fungitell assay)	Baseline, week 6, week 12	I-FABP, LPS, and β-D-glucan are established indicators of gut epithelial damage and bacterial and fungal translocation
Inflammatory/anti-inflammatory cytokines	IL-1β, IL-6, IL-8, IL-17A/F, IL-22, IL-10, IL-37, IP-10	Change from baseline, compared between FMT and placebo arms	Mean/median (Multiplex or ELISA)		Evaluates whether FMT could reduce immune activation and decrease the risk of non-AIDS comorbidities
Immune cell activation	Flow cytometry of HLA-DR, CD38 on T-cells, CD83, CD86 on myeloid cells	Change from baseline, compared between FMT and placebo arms	Mean/median		
c. Exploratory outcomes					
Outcome	Measurement variable(s)	Analysis metric	Method of aggregation	Time points	Clinical relevance
Microbiota composition and diversity	16S, 18S rDNA sequencing, metagenomics in stool samples	Change from baseline, compared between FMT and placebo arms	Alpha/beta diversity metrics; LEfSe; DESeq2	Baseline, week 6, week 12	Identifies changes in microbiota profile
HIV reservoir size (blood and gut)	Quantitative PCR on sorted CD4 T cells	Fold change from baseline, compared between FMT and placebo arms	Mean/median	Baseline, week 12	Potential for reducing latent HIV reservoir, supporting cure strategies
Engraftment analysis	Comparison of donor and recipient microbiota (16S/18S/metagenomics)	Similarity analysis	Proportion/shared taxa	All fecal sample time points	Measures the success of microbial transplantation
d. Sub-study outcomes (optional colon biopsies)					
Outcome	Measurement variable(s)	Analysis metric	Method of aggregation	Time points	Clinical relevance
Gut mucosa architecture	Immunostaining for claudin-3, occludin	Comparison pre-/post-intervention, compared between FMT and placebo arms	Microscopic evaluation	Baseline 2, week 12	Evaluates epithelial integrity, a key factor in preventing microbial translocation
Mucosal immune activation	Flow cytometry on colon biopsy cells (CD38, HLA-DR on T-cells, CD83, CD86 on myeloid cells); qPCR for cytokines	Change from baseline, compared between FMT and placebo arms	Mean/median		Measures direct effects of FMT on gut immune environment
HIV reservoir in gut CD4 T cells	qPCR on CD4 T cells from biopsies	Fold change, compared between FMT and placebo arms	Mean/median		Assesses FMT’s effect on mucosal HIV persistence

The primary endpoint for analysis will be at weeks 6 and 12.

The efficacy outcomes (REG3α, cytokines, immune activation) assess whether FMT can reduce chronic immune activation, enhance gut integrity, and potentially impact the HIV reservoir, all of which are key to improving long-term health in PWH.

On the other hand, the harm outcomes (safety, tolerability) ensure that any potential risks associated with FMT are detected and managed promptly, particularly given the immune status of participants.

### Participant timeline {13}

The study flow chart shows the time schedule of enrollment, interventions, assessments, and visits for participants.

### Sample size {14}

A total of 20 PWH participants will be enrolled, randomized 1:1 into two groups: FMT group (10 participants) and placebo group (10 participants).

The influence of gut microbiota targeting therapies on REG3α levels has not been tested yet. Hence, we calculated that based on the difference in REG3α levels between ART-treated (2441 ± 630 pg/mL) and HIV-negative controls (715 ± 243 pg/mL) [36], a sample size of 5 participants per group would allow 80% power to observe an effect, with a *p* value of 5% (https://clincalc.com/stats/samplesize.aspx). The clinical assumption and hypothesis is that complete change in the gut microbiota towards the one of HIV-negative controls would lower REG3α levels to those of controls. However, as previous FMT trials did not obtain 100% engraftment of the donor microbiota, sample size per group was doubled with 10 participants per arm. Due to the exploratory nature of the study, the small sample size is considered sufficient to detect preliminary signals in biomarkers of gut permeability, immune activation, and microbial translocation. Our study will inform larger, future randomized controlled trials as the variability in outcomes like REG3α, inflammatory markers, and microbiota composition will be estimated to support future power calculations.

As for the sub-study sample size, the optional colon biopsy sub-study includes a subset of the main study participants. No specific target number for this subgroup is defined, but participants must first qualify for and consent to the main study. In previous trials, around 50% of participants agreed to partake in the sub-study with colonoscopy as it can benefit participant with cancer screening [44–46].

### Recruitment {15}

Some of the recruitment strategies to achieve the target sample size of 20 participants are outlined below:In-clinic recruitment by study team: The qualified investigator ([name]) and study staff will identify eligible participants directly from the clinical HIV cohort at the CVIS. This clinic provides care to more than 2000 PWH, offering a robust recruitment base.Direct outreach to potential participants: Study staff will explain the study and its procedures to prospective participants during clinic visits. They will review inclusion and exclusion criteria and discuss the voluntary nature of participation.Promotional activities by investigators: Teleconferences and in-person meetings will be held with the research team to coordinate and encourage recruitment. The sponsor investigator and qualified investigator will promote the study at local medical meetings and HIV conferences (e.g., CTN semi-annual meetings). Study has been advertised by the Montreal LGBTQ journal *Fugues*. A quick video explaining the study rationale was prepared (https://www.ctnplus.ca/study/ctnpt-038-the-gutsy-study/).

## Assignment of interventions: allocation

### Sequence generation {16a}

Participants are assigned to one of two arms: FMT capsules (group 1) or placebo capsules (group 2) allocated with 1:1 ratio.

#### Method of randomization

A statistician developed the randomization list prior to study commencement. A statistician will generate a list of random allocations in blocks using the PLAN procedure in Statistical Analysis System (SAS) software. The generated allocation sequence sequentially included in numbered sealed envelopes containing the group assignment. The number of placebo capsules, ranging from 30 to 40 per dose, is randomly selected based a uniform distribution using the RANUNI Function.

#### Blinding design

The study is single-blind so participants are blinded to the group assignment. Study staff who enroll participants are not blinded, but the sequence is concealed until after participant eligibility is confirmed.

### Concealment mechanism {16b}

The allocation sequence is implemented using sequentially numbered, sealed envelopes. These envelopes are prepared in advance by the CIHR/CTN statistician. Each envelope contains the randomization group assignment (FMT or placebo). Envelopes are opened only after the participant is screened and confirmed eligible for the study ensuring the allocation sequence is concealed from enrolling staff until the point of assignment.

### Implementation {16c}

A statistician designated by the study team generated the randomization list before study initiation. Study staff under the supervision of the qualified investigator ([name]) at the McGill University Health Centre (MUHC), Glen Site, is in charge of enrolling participants. Once enrolled, study staff open the next sequentially numbered, sealed envelope after confirming participant eligibility to determine group assignment (FMT or placebo). The randomization group is recorded in the electronic case report form (eCRF) after envelope opening.

## Assignment of interventions: blinding

### Who will be blinded {17a}

Table 2 shows a summary of blinding assignment.

**Table 2 Tab2:** Summary of blinding assignment

Blinded role	Blinded?	How blinding is maintained
Trial participants	Yes	Participants are not told whether they are receiving FMT or placebo capsules. Both capsule types are identical in appearance, weight, and color
Care providers	No	Study staff administering capsules are aware of group assignments after opening randomization envelopes
Outcome assessors	No	Not explicitly stated; however, since the same staff may conduct follow-up, they may not be blinded
Data analysts	No	No indication in the protocol that data analysts will be blinded

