#### Reference to statistical analysis plan

Further details on statistical procedures, variable definitions, and subgroup analyses are described in the Statistical Analysis Plan (SAP) maintained separately from the protocol. The SAP will be finalized prior to database lock and is available upon request.

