#### Other committees

Data management and laboratory operations are handled by the MUHC Research Institute and collaborating research laboratories in London, ON. These teams are responsible for sample processing, secure data storage, and maintaining data quality standards.

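### Table 2 leaves outcome assessors and data analysts unmasked without a reason or safeguard, although coded samples make masking feasible at little cost

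*Protocol article*

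**What the plan says.** All references are to the protocol article.

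- **Who will be blinded {17a}, Table 2.** Participants are blinded and care providers are not. Outcome assessors are marked No, with the comment "Not explicitly stated; however, since the same staff may conduct follow-up, they may not be blinded". Data analysts are marked No, with the comment "No indication in the protocol that data analysts will be blinded".
- **Implementation {16c}.** "The randomization group is recorded in the electronic case report form (eCRF) after envelope opening".
- **Reference to statistical analysis plan.** "The SAP will be finalized prior to database lock and is available upon request". Trial status says that recruitment ended in August 2025 and data collection continues.
- **Outcomes {12}, Table 1.** The aggregation entry for REG3α is "Mean or median (analyzed using *t*-test or Wilcoxon rank sum test"). The text below the table names weeks 6 and 12 together as the primary endpoint. Primary outcome analysis names baselines 1 and 2 without saying how they combine.
- **Data security and storage; Access and sharing.** Biological sample data, and data passed to laboratories, are linked to study IDs only. Access to the eCRF is by role.
- **Data quality assurance.** Flow cytometry gating is described as validated. Nothing says that it is done without knowledge of the arm.

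**The concern.** A single-blind design explains why the staff who give the capsules know the arm. It does not explain why people who never meet the participant, such as the cytometry operator, the biopsy reader and the statistician, should know it. Table 2 gives no scientific reason for either No; its comments read as if the matter had not been decided.

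Two kinds of bias are at stake. A reader who knows the arm can shift a result that depends on judgement. An analyst who sees the arm can, without intending to, settle open choices in the direction that favours the hypothesis. The trial is meant to inform the size of later trials, so a signal that could be explained in either way would be a weak basis for planning.

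**Working it through.** The plan gives no figure for this point. The check sets the passages side by side and then asks what a simulation can and cannot show.

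**1. Which outcomes depend on judgement?**

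| Outcome | Read-out | Exposed to a reader who knows the arm? |
|---|---|---|
| REG3α (primary) | ELISA | Little |
| I-FABP, LPS, β-D-glucan, cytokines, chemistries | Assay read-outs | Little |
| T-cell and myeloid activation | Flow cytometry, validated gating | Some; masking not stated |
| Biopsy architecture (optional sub-study) | Microscopic evaluation | Yes |
| Adverse event intensity and causality | Graded by staff | Yes |

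**2. Is masking feasible?** Samples are coded and eCRF access is already by role. What is missing is a statement that the link from study ID to arm is withheld from readers and the analyst. A study ID protects the participant's identity. It masks the arm only if that link is closed, and the arm sits in the same eCRF.

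**3. Does the analyst have choices to make?** The article leaves open two tests (t or rank), two visits (week 6, week 12) and up to three baselines (baseline 1, baseline 2, their mean).

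Simulation with no true effect:
- From the article: 10 per arm and two-sided α = 0.05.
- Assumed: within-person correlation 0.3, 0.7 or 0.9, equal between all visits; normal or lognormal data.
- 4,000 runs per setting. A false positive is counted when the smallest p-value among the permitted analyses is below 0.05.

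| Permitted analyses | Number | False-positive rate |
|---|---|---|
| One t-test, one visit, mean baseline | 1 | about 4 to 5% |
| t or rank, one visit | 2 | about 5 to 6% |
| t-test, either visit | 2 | about 8 to 10% |
| t or rank, either visit | 2 × 2 = 4 | about 10 to 11% |
| As above, mean baseline or baseline 2 | 2 × 2 × 2 = 8 | about 14 to 17% |
| As above, any of three baselines | 2 × 2 × 3 = 12 | about 19 to 21% |

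Monte Carlo standard error is √(0.05 × 0.95 / 4000) = 0.3 percentage points near 5%, and √(0.2 × 0.8 / 4000) = 0.6 points near 20%.

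**4. Would A/B coding lower these rates?** No. Swapping the labels turns t into −t and U into 10 × 10 − U, so every two-sided p-value is unchanged. An analyst who sees only A and B can still find the smallest p-value. Coding prevents choosing by direction, that is, by whether a result favours FMT. Only fixing test, visit and baseline returns the rate to about 5%.

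**The case against.** The strongest reply is that this is an openly declared single-blind pilot of 20 people. Its primary outcome is an ELISA, duplicate testing of critical assays is planned where feasible, gating is validated, and the detail belongs to a SAP that is not shown. Signing a SAP before database lock is ordinary practice. Most of this stands, and it limits the point. SAP content that is not shown is not a finding, and nothing in the article says that analysts have received outcome data by arm. The blinding status, however, is not left to the SAP: Table 2 states it. Signing before lock also protects less when the analyst may already see the arm.

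A reader might infer more, and the documents do not support it:

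- **That every endpoint is biased by assessors.** The primary and most soluble markers are assay read-outs.
- **That flow gating is still open.** It is described as validated; only masking to arm is unstated.
- **That allocation reaches the bench through London.** Capsules are made there, and laboratories there handle some operations. No text says that bench staff learn the arm.
- **That different storage temperatures defeat the blinding.** Storage precedes dispensing by staff who are unblinded anyway. No text says that participants can notice, and it has no bearing on assessors or analysts.
- **That unblinding raises the false-positive rate to about 20%.** Step 4 shows that this rate comes from unfixed choices, and it assumes that someone always takes the smallest p-value.

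**Conclusion.** The point holds in limited form. By the article's own table, assessors and analysts are not masked, no reason or safeguard is given, and masking is within easy reach. The exposure lies mainly in flow cytometry reading, biopsy microscopy, adverse event grading, and analysis choices made with the arm visible before the SAP is final.

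The bias from unmasked reading or analysis cannot be quantified from the document. Sample size, power and nominal α do not change. The rates above are a separate worst case for choices not yet fixed, under assumed correlations and distributions; they do not show that such selection will occur. For assessors, Table 2 hedges its No, so their actual status also needs to be settled.

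The change is worth making because it is cheap and, with data collection still in progress, can still be applied to any assays and analyses not yet done.

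**What to change.** 1. **Laboratory and biopsy readers.** Change Table 2 so that they work on coded samples without access to allocation. Except the donor-recipient engraftment analysis where the comparison itself reveals the arm.
2. **Analyst.** Withhold the eCRF allocation field and supply arms as A and B until the SAP and the primary analysis code are signed.
3. **SAP.** Sign it before any outcome data are viewed by arm, naming one primary test, one baseline definition and one primary time point. This step, not the coding, controls the false-positive rate.
4. **Adverse events.** State that causality is graded by staff who know the arm, so that the safety comparison is read accordingly.
5. **Work already done.** If any assay or analysis has been completed unmasked, report which.

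Cost: an access restriction, a coding step and an earlier SAP signature. The downside is that a person outside the analysis must hold the arm key.
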